## Abstract

**Background:**

Androgen deprivation therapy (ADT) improves outcomes in men undergoing definitive radiotherapy for prostate cancer but carries significant toxicities. Clinical parameters alone are insufficient to accurately identify patients who will derive the most benefit, highlighting the need for improved patient selection tools to minimize unnecessary exposure to ADT’s side effects while ensuring optimal oncological outcomes. The ArteraAI Prostate Test, incorporating a multimodal artificial intelligence (MMAI)-driven digital histopathology-based biomarker, offers prognostic and predictive information to aid in this selection. However, its clinical utility in real-world settings has yet to be measured prospectively.

**Methods:**

This multicentre implementation trial aims to collect real-world data on the use of the previously validated Artera MMAI-driven prognostic and predictive biomarkers in men with intermediate-risk prostate cancer undergoing curative radiotherapy. The prognostic biomarker estimates the 10-year risk of metastasis, while the predictive biomarker determines the likely benefit from short-term ADT (ST-ADT). A total of 800 participants considering ST-ADT in conjunction with curative radiotherapy will be recruited from multiple Australian centers. Eligible patients with intermediate-risk prostate cancer, as defined by the National Comprehensive Cancer Network, will be asked to participate. The primary endpoint is the percentage of patients for whom testing led to a change in the shared ST-ADT recommendation, analyzed using descriptive statistics and McNemar’s test comparing recommendations before and after biomarker testing. Secondary endpoints include the impact on quality of life and 5-year disease control, assessed through linkage with the Prostate Cancer Outcomes Registry. The sample size will be re-evaluated at an interim analysis after 200 patients.

**Discussion:**

ASTuTE will determine the impact of a novel prognostic and predictive biomarker on shared decision-making in the short term, and both quality of life and disease control in the medium term. If the biomarker demonstrates a significant impact on treatment decisions, it could lead to more personalized treatment strategies for men with intermediate-risk prostate cancer, potentially reducing overtreatment and improving quality of life. A potential limitation is the variability in clinical practice across different centers inherent in real-world studies.

**Trial Registration:**

Australian New Zealand Clinical Trials Registry, ACTRN12623000713695p. Registered 5 July 2023.

**Supplementary Information:**

The online version contains supplementary material available at 10.1186/s12885-025-13622-1.

## Background

Prostate cancer is the most commonly diagnosed male malignancy, with over 24,000 cases diagnosed in Australia in 2021 [1]. It is responsible for the highest incidence of cancer-related disability worldwide, with a large proportion of such morbidity because of the adverse outcomes associated with over-treatment or under-treatment [2]. Radiotherapy is commonly employed to cure localised disease, with androgen deprivation therapy (ADT) reserved for treatment intensification of higher stage disease [3]. ADT has toxicities, with the potential to reduce quality of life and cause adverse health outcomes [4]. The challenges for treatment intensification lie in accurate prognostication, with a multitude of tumour, patient, and treatment factors also impacting outcomes.

The National Comprehensive Cancer Network (NCCN) risk classification has helped improve prognostication for localised prostate cancer and remains a widely used tool to guide management [5]. This system is imperfect, with overlapping outcomes between risk groups, as well as a wide range of possible disease control rates within each risk classification, and several alternative systems such as CAPRA have been proposed [6, 7]. Issues of variability and subjectivity can enter into some of the parameters, such as histopathological grading, weakening the prognostic ability. The Gleason scale was developed over half a century ago and has shown ambiguity in reproducibility across expert uropathologists [8]. Decipher, a tissue-based genomic biomarker assessing 22 genes, has shown improved prognostication but lacks validation in prospective randomized trials [9]. There also remain challenges with consumptive pathology tests such as cost, laboratory requirements, processing time, and tumour representation. A deeper issue is that even if a patient with a worse prognosis is identified, whether treatment intensification is likely to benefit that specific individual is unknown. It is therefore important to develop predictive biomarkers to help determine if a specific intervention, such as ADT, will lead to additional efficacy for such an individual.

Several randomized controlled trials (RCTs) have investigated the use of short-term ADT (ST-ADT) in intermediate-risk prostate cancer, including RTOG-9408, EORTC 22,991, DFCI 95–096, and RTOG 0815 [3, 10–13]. While some of these trials have demonstrated improvements in biochemical control and, in some cases, reductions in distant metastases and cancer-specific mortality with the addition of ST-ADT, they often suffer from limitations such as the use of older radiotherapy techniques, heterogeneous patient populations, and an inability to precisely identify the subpopulation most likely to benefit from ADT. The D’Amico RCT highlighted comorbidity as a potential discriminator, suggesting that patients with moderate to severe comorbidities may not benefit from ST-ADT and may experience increased cardiac mortality [11, 12]. These findings underscore the need for better tools to guide personalized treatment decisions regarding ST-ADT in intermediate-risk prostate cancer.

The ArteraAI Prostate Test uses a multimodal AI (MMAI) architecture that encompasses both clinical and digital histopathology data. Multimodal deep learning uses combinations of various data modalities together, compared to a singular modal learning which would analyse each of these independently. The clinical features of this model consist of: age, PSA, Gleason combined, Gleason primary, Gleason secondary, and T-stage. The second pipeline consists of digital histopathology, which was trained using a self-supervised learning model. This analyzes multiple image features using a neural network. Both the clinical and histopathology vectors are analysed together using a separate neural network to create a MMAI score, Fig. 1.

The ArteraAI Prostate Test is a unique clinicopathological biomarker test which utilises the MMAI architecture described to run two models: a prognostic model and a predictive model. Firstly, the prognostic model provides estimates of distant metastasis (DM) and prostate cancer-specific mortality (PCSM) risk. The prognostic deep learning model was trained and validated on 5 phase III randomised control trials (NRG/RTOG 9202, 9408, 9413, 9910, and 0126), with a total of 5,654 patients and a dataset of 16,204 histopathology slides. This model was shown to significantly outperform the NCCN classification with a 5-year distant metastasis AUC of 0.83 compared to 0.72 for NCCN, *p* < 0.001 [14]. The predictive model assesses the benefit of short-term, 4–6 months of ADT (ST-ADT) in intermediate-risk (IR) prostate cancer patients and has recently been validated. In the predictive model positive patients, ST-ADT significantly reduced the risk of distant metastasis compared to radiotherapy alone (sHR = 0.34, 95% CI 0.19–0.63, *p* < 0.001). There were no significant differences with the addition of ADT in the predictive model negative subgroup (sHR = 0.92, 95% CI 0.59–1.43, *p* = 0.71) [15].

The test can inform the shared ST-ADT discussion between clinicians and patients on the benefit ADT may have in men being managed with definitive RT for IR prostate cancer. The real-world data on the impact of this test in clinical practice is currently lacking, which is the main question we are exploring via ASTuTE.

**Fig. 1 Fig1:**
[figure not shown]
Development of a Multimodal Artificial Intelligence Tool in Prostate Cancer

## Design

The ASTuTE trial (*A*rtificial intelligence *S*teering *T*estosterone deprivation *T*reatments in prostate cancer *E*xternal-beam radiotherapy) is an open-label, multicentre, prospective registry and trial of implementation that aims to collect real world data on the use of a MMAI-driven biomarker digital histopathology test developed by Artera^®^ for use in IR prostate cancer men undergoing curative radiotherapy.

The trial was designed by the authors, using the SPIRIT-AI extension recommendations [16], and was devised to assess the impact of the ArteraAI Prostate Test on shared ST-ADT decisions. The trial was first registered with the Australian Clinical Trials Registry (ACTRN12623000713695) on 5 July 2023. Central ethical approval was obtained from St Vincent’s Human Research Ethics Committee (HREC 2023/ETH01630) in 2023, with the first patient enrolled December 2023. Local ethical and governance approval has been obtained from all participating sites. The study is being conducted in accordance with the Declaration of Helsinki, the National Health and Medical Research Council (NHMRC) National Statement on Ethical Conduct in Human Research 2007 and the NHMRC Australian Code for Responsible Conduct of Research. All participants are providing written informed consent.

The primary goal of this study is to create a de-identified database of patients, test results, and treatment decisions that can be queried to determine the clinical utility of the MMAI digital histopathology test known as ArteraAI Prostate Test, in the utilisation of ST-ADT for men with IR prostate cancer. Eligible participants will undergo data collection as per Fig. 2. For patients that will receive radiotherapy, all curative intent radiotherapy dose/fractionation schedules are allowed including conventional [17], moderately hypofractionated [18] and ultra-hypofractioned [19] as well as dominant intraprostatic lesion (DIL) boosting [20]; this will enable data generalizability across modern techniques.

**Fig. 2 Fig2:**
[figure not shown]
ASTuTE study schema

### Endpoints

The primary objective is to assess the impact of the ArteraAI Prostate Test on shared ST-ADT decisions with IR prostate cancer men undergoing curative radiotherapy. To evaluate this, the endpoints of shared ST-ADT decisions pre-test and post-test will be recorded. The primary endpoint is the percentage of cases with changes in ST-ADT shared decision recommendations.

The secondary objectives will be assessed through linkage with the Prostate Cancer Outcomes Registry (PCOR) and will assess efficacy and quality of life. The secondary endpoint of efficacy will be assessed at 5 years using the Phoenix criteria of PSA nadir + 2ng/mL [21], and/or initiation of salvage treatment and/or imaging confirming recurrent disease. The secondary endpoint of quality of life will be assessed using the Expanded Prostate Cancer Index Composite questionnaire (EPIC-26).

The primary hypothesis is that the ArteraAI Prostate Test will result in changes to ADT management of IR prostate cancer patients. The secondary hypotheses are that this will be accompanied by ongoing high rates of disease control and improved quality of life for those spared ADT.

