### Methods

After providing informed consent, clinical variables including combined Gleason score, Primary Gleason Score, Secondary Gleason Score, clinical T-stage, baseline PSA, and age at biopsy are recorded. Next, a single formalin fixed, paraffin embedded (FFPE) hematoxylin and eosin-stained slide containing one biopsy core with the tumor that has the highest Gleason grade used by the local pathologist in making their diagnosis for the patient will be digitised.

When scanning is completed, a certified pathologist approved by Artera^®^ will review the digitally converted image to assess suitability for the MMAI biomarker test. The test will be run using locked AI models (v1.2) for the duration of the study. The locked models makes sure all participants will be assessed using the same models [23]. After completion of the test, the ArteraAI Prostate Test report will be verified by the certified pathologist and then made available to clinical staff via a web portal.

Figure 3 shows an example of the test report. Figure 3a displays an example of an NCCN unfavourable IR prostate cancer who is estimated to have a low prognostic risk for distant metastasis and low predictive benefit for the addition of ADT with radiotherapy using the ArteraAI Prostate Test. Figure 3b displays the other side of the spectrum with the ArteraAI Prostate Test estimating a high prognostic risk for distant metastasis and high predictive benefit for the addition of ADT with radiotherapy. Before the test result is available, the pre-test shared ADT decision result is captured. After the ArteraAI Prostate Test results are discussed between the clinician and patient, the post-test shared ADT decision result will be recorded. At a median follow-up of 5 years for the cohort, a data linkage with PCOR will be established to allow for assessment of quality of life and efficacy data (Table 2).

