### Statistical considerations

Given the novel nature of ASTuTE, it is not possible to estimate the event rate for the primary endpoint proportion change in shared decision making regarding use of ADT. If an incorrect estimate is used, there is a risk of underpowering the study. Therefore, an interim analysis will be performed at 200 participants. This will allow for early assessment into the rates of management change and help determine the final number of participants needed to adequately power the final analysis of the study. At this time, 800 participants are planned for enrolment, with final numbers to be determined at the time of the interim analysis.

The McNemar’s test will be used to analyse the primary endpoint. There is a rare chance that the number of pre- to post-test recommendations of Yes-No and No-Yes is equal. This could lead to the null hypothesis being retained when the ArteraAI Prostate test is actually outperforming standard of care. As such, the study is designed to be hypothesis-generating, rather than focusing on a specific hypothesis that would define the sample size. This trial of implementation which assesses rates of management change based on a biomarker test has been used in recent literature. The DCISionRT^®^ study, used this approach to assess a breast genomic biomarker impact on radiation therapy recommendations [24].

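### The abstract promises to determine the test's impact on quality of life and 5-year disease control, but the design identifies impact on decisions only, and the secondary hypotheses name neither a reference value nor a clear group.

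*Protocol article*

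**What the plan says.** The Abstract (Discussion paragraph) states that "ASTuTE will determine the impact of a novel prognostic and predictive biomarker on shared decision-making in the short term", and the same sentence goes on to "both quality of life and disease control in the medium term". The Abstract (Methods paragraph) agrees: "Secondary endpoints include the impact on quality of life and 5-year disease control".

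The Design section describes an "open-label, multicentre, prospective registry and trial of implementation", with no untested arm. The Methods section says of the AI version used: "The locked models makes sure all participants will be assessed using the same models". So all men receive the test. The comparison the plan names is McNemar's test "comparing recommendations before and after biomarker testing".

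In the Endpoints section, the secondary hypotheses are that changes in ADT management will be accompanied by "ongoing high rates of disease control and improved quality of life for those spared ADT". Both secondary outcomes come from registry linkage. The Data analysis plan gives secondary analyses summary statistics, and the text after Fig. 4 applies logistic regression to the pre-test and post-test recommendations, not to disease control or EPIC-26. The main Discussion is more modest than the Abstract and promises only stronger prospective efficacy data.

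**The concern.** A before-after comparison of recommendations works for the primary endpoint because each man supplies both values. It cannot work for outcomes. Each man has one disease course and one quality-of-life course, both under his post-test decision. What would have happened under the pre-test decision is never seen, and no untested, historical or registry comparator is stated in its place.

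Two features of the hypothesis wording add to this. First, without a reference value almost any observed control rate could be called high. Second, men spared ADT could mean everyone with a post-test No. That mixes men the test moved off ADT with men who were not going to have it anyway. Comparing post-test No with post-test Yes would also be confounded, because the test result informs the post-test decision.

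What is at stake is a reassuring five-year rate being read as evidence that omitting ADT on the test result costs nothing. The article's own figures leave that open: in predictive-negative men the effect of ADT on distant metastasis is given in the Background as sHR 0.92 (95% CI 0.59 to 1.43), which does not exclude a material lost benefit.

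**Working it through.** **Claim against design.** The plan gives no alpha, power, effect size or margin for any secondary outcome, and the sample size is provisional ("800 participants are planned for enrolment, with final numbers to be determined at the time of the interim analysis"). There is no planned figure to reproduce. The first step is therefore a comparison of texts.

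| Item | Decision endpoint | Disease control, EPIC-26 |
|---|---|---|
| Value under the pre-test plan | Recorded | Not observed |
| Value under the post-test plan | Recorded | Observed at 5 years |
| Stated comparison | McNemar, pre versus post | None |
| Stated reference | Pre-test decision | None |

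The word impact is supported in the first column and not in the second.

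**Dilution, if a whole-cohort rate is reported.** The documents give no five-year failure rate, switched share or harm size for this trial. The following are assumptions:

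- Five-year failure with ADT: 10% (range considered 5% to 15%).
- Share of all men switched Yes to No: 20% (range 10% to 29.3%).
- Added failure risk in those men: 5 points (10 points, a doubling, also shown).

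The 29.3% is borrowed from the DCIS biomarker study in the main Discussion. If its 46% and 35% are read as rates within the pre-test Yes and pre-test No groups, the pre-test Yes share p solves 0.46p + 0.35(1 − p) = 0.42. So p = 0.07/0.11 = 63.6%, and 0.46 × 0.636 = 29.3%, or about 234 of 800.

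Formulas:

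- Cohort shift = switched share × added risk.
- 95% half-width = 1.96 × √(p(1 − p)/n).
- Power against a fixed benchmark: normal approximation, two-sided 5%.

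Central case:

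- Switched men: 0.20 × 800 = 160.
- Cohort shift: 0.20 × 5 = 1.0 point, from 10.0% to 11.0%.
- Cohort half-width: 1.96 × √(0.10 × 0.90/800) = 2.1 points.
- Switched men alone: 15% ± 1.96 × √(0.15 × 0.85/160) = 15% ± 5.5 points.

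At 10% baseline failure:

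| Switched share (n) | Added risk | Cohort shift | Power, cohort vs 10% | Power, switched men vs 10% |
|---|---|---|---|---|
| 10% (80) | +5 | 0.50 | 7% | 35% |
| 20% (160) | +5 | 1.00 | 16% | 55% |
| 29.3% (234) | +5 | 1.46 | 29% | 69% |
| 10% (80) | +10 | 1.00 | 16% | 78% |
| 20% (160) | +10 | 2.00 | 47% | 95% |
| 29.3% (234) | +10 | 2.93 | 76% | 99% |

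At +5 points the shift stays below the half-width at every switched share, and also at baselines of 5% (half-width 1.5) and 15% (half-width 2.5). In the last row the cohort rate is 12.9% ± 2.3, which excludes 10%.

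**Offsetting.** If 20% switch Yes to No with 5 added points of failure, and 10% switch No to Yes with 10 fewer points, the net shift is 0.20 × 5 − 0.10 × 10 = 0.0. A flat cohort rate can therefore conceal movement in both directions.

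These half-widths assume complete five-year status for all 800 men. Linkage is planned at a median follow-up of five years, so real intervals would be wider.

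**The case against.** The strongest reply is that the operative text is already cautious. The Endpoints section says the objectives will assess efficacy and quality of life, and that outcomes will accompany the changes, which is the language of association. The Statistical considerations section calls the study hypothesis-generating. The population for a secondary analysis, and the exact meaning of spared, may sit in a full protocol or analysis plan that is not shown. This stands as far as it goes: the absence of subgroup detail is not itself the finding. It does not rescue the Abstract, whose causal wording has no stated support.

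A reader might also infer four stronger things that the documents do not support:

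- **That disease control will be reported only for the whole cohort.** The article never fixes this, and the hypothesis itself refers to a subgroup. The dilution argument is conditional.
- **That only Yes-to-No men can be harmed by the test.** They are the ones exposed to harm from omitted ADT. No-to-Yes men are exposed to ADT toxicity because of the test, and quality of life is one of the outcomes.
- **That a cohort rate could not reveal even a doubling of failure.** It depends on the switched share, as the last row of the table shows.
- **That an untested randomised arm would settle the matter.** Read over all men, it is diluted in the same way. For 10% versus 11%, 80% power needs about 14,750 per arm, and 400 per arm gives about 7%.

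**Conclusion.** The point holds as a mismatch between stated aim and design. The trial can determine the test's impact on shared decisions. It can describe, but not determine the impact on, quality of life and disease control. This part needs no assumptions and rests on the Abstract, Design, Methods and Data analysis plan read together. The lack of a reference for high rates and the ambiguity of the spared group also follow directly from the Endpoints wording.

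The size of the dilution is illustrative. Under the central assumptions, a 5-point excess in the switched men is a 1.0-point shift in the cohort, with about 16% power against a fixed 10% benchmark, compared with 55% in the switched men alone. Every failure rate, switched share and harm size here is assumed or borrowed. The finding does not say that 800 is the wrong number; the article gives no inputs from which to judge it.

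**What to change.** 1. In the Abstract (Methods and Discussion paragraphs), keep the causal verb for decisions and use describe or estimate for quality of life and disease control.
2. In the Endpoints section, define men spared ADT as pre-test Yes and post-test No.
3. Report 5-year disease control and EPIC-26 with confidence intervals for all four cells of the Fig. 4 table. Name Yes-to-No as the key cell for omitted ADT and No-to-Yes as the key cell for added ADT toxicity.
4. State in advance the reference value against which high rates will be judged, and its source. A single-cell rate with an interval still needs one.
5. If Yes-to-No is compared with Yes-to-Yes, adjust for baseline EPIC-26 and clinical covariates and label the result descriptive, because the test result largely drives who switches. This would be a new model: the covariates now listed are for the recommendation models, and baseline EPIC-26 is not among them.

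The cost is more modest claims and a little more analysis. The decision cells are already being recorded, and no new patients are needed.
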